## Abstract

**Background:**

Total hip arthroplasty (THA) is an increasingly common treatment for older patients with hip osteoarthritis. The best strategy for a physiotherapy intervention for older people after THA is not clear in the literature. The purpose of this protocol study is to test the feasibility of undertaking a full trial clinical to evaluate the effect of ergometer cycling-associated conventional exercises on functional results and health-related quality of life (HRQOL) of older patients with THA.

**Methods/Design:**

This study protocol is a prospective, single center, randomized controlled pilot clinical trial. Older patients (≥60 years) in the postoperative phase after primary unilateral THA for hip osteoarthritis will be consecutively recruited for this study and randomly allocated to 2 treatment groups. Group I will perform cycle ergometer and conventional exercises, and group II will perform only conventional exercises. The sessions will be conducted twice a week for 8 weeks. Assessments will be made at baseline (2 weeks postoperatively: the moment that the patients receive a referral for physical therapy, which will start after suture removal), after intervention (10 weeks postoperatively), and at 6 months of follow-up (24 weeks postoperatively). The primary outcomes are the function, evaluated using the Harris Hip Score (HHS) and the Short Physical Performance Battery (SPPB). The secondary outcome is HRQOL, measured using 2 evaluation instruments: the Medical Outcomes Study 36-Item Short-Form Health Survey (SF-36) and the Western Ontario and McMaster Universities Osteoarthritis Index (WOMAC). Data collectors will be blinded and will not have contact with participants during the interventions.

**Discussion:**

This randomized controlled trial will provide evidence regarding the effect of this exercise therapy on physical function and quality of life in older patients after THA. If our hypothesis is correct, both interventions will be effective, but the exercises on the cycle ergometer conferring better results in function, physical performance and quality of life. The study follows Consolidated Standards of Reporting Trials (CONSORT) guidelines, and the approval of the local ethics committee has been obtained.

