### Objectives and hypotheses

The aims of this prospective, single center, randomized controlled pilot study are:to test the feasibility of undertaking a full trial clinical;to identify if the cycle ergometer will be well tolerated by older patients with THA in the early phase of rehabilitation;to test the feasibility of the proposed outcome measures;to identify effect size at end of treatment in order to calculate an appropriate sample size for the full trial clinical.

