### Statistical analysis

To describe the sample profile descriptive statistics of numerical variables (scores of scales) will be made.

To compare numerical variables between the two groups at baseline we will use the Mann-Whitney test, due to lack of normal distribution of variables. To compare longitudinal measures between groups and times we will use analysis of variance (ANOVA) for repeated measures, followed by Tukey’s multiple comparison test to compare the groups at all times, and the profile test contrasts to analyze the evolution between assessments in each group. The variables will be transformed into posts (ranks) in the absence of normal distribution.

To estimate the sample size and the power of the sample we will use the sample size calculation for longitudinal studies with repeated measures to compare variables between the two groups (I and II) over the two collection times (pre and post intervention). The significance level will be defined (alpha or Type I error) at 5%, calculating the effect size or delta, which is the expected difference or difference obtained between the group means divided by the standard deviation, and the coefficient of intraclass correlation between repeated measurements. The values of the effect size delta (delta effect size) will vary generally between 0 and 3. Delta values of 0.25, 0.75 and 1.25 respectively correspond to small, medium or large effects. Subsequently, the power of the sample and the sample size will be obtained by setting the power at 80% or Type II error (1-beta) at 20%. The significance level for statistical tests will be 5% (*P* < 0.05).

Statistical analysis of the data will be performed using SAS® software, Version 9.1.3 for Windows (SAS Institute Inc., Cary, NC, USA).

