Some problems and limitations in conducting this trial may interfere with its effect. First, we emphasize that the participants in the intervention and the applicator will not be blinded. Second, participants in the control group, who will not perform cycle ergometer-associated exercises, will know when reading the consent form that this resource will not be used for their rehabilitation but will be used by other patients with the same condition. This may generate some disincentive; however, this feature will be offered to the control group after 10 weeks postoperatively.

Loss to follow-up may occur over the course of the study and may be considered a third limitation. The study will be conducted at a regional referral hospital where patients from neighboring cities are treated. Difficulties in transporting patients to physical therapy sessions can lead to missed sessions or the inability to continue rehabilitation at this institution. In these cases, referrals and guidance will be given for rehabilitation services in neighboring towns and patients will return to the study institution only for clinical follow-up.

Another consideration is that the exclusion criteria limit the generalization of the results to other populations. Even in the case of a pilot clinical trial, the results may not be generalized to patients with THA who are unable to perform moderate-intensity exercise, such as in cases of cardiovascular complications in the postoperative period.

This randomized clinical trial has been designed with the main purpose of evaluating the feasibility of undertaking a trial to compare the effect of cycle ergometer-associated conventional exercises to conventional exercises alone in older patients with THA. The results of the pilot trial will be used to inform the design of the future definitive study, which would provide evidence relating to the inclusion of this resource in the functional recovery of these patients. In accordance with CONSORT guidelines for reporting of clinical trials, the results will be submitted to a peer-reviewed international journal for publication irrespective of the outcome.

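### The abstract says this pilot will itself supply evidence on the ergometer's effect, while the stated aims and the main Discussion leave that evidence to a later trial

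*Protocol article*

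**What the plan says.** The protocol article describes the purpose of the trial in several places.

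- **Abstract, Background:** "The purpose of this protocol study is to test the feasibility of undertaking a full trial clinical to evaluate the effect" of adding ergometer cycling to conventional exercises.
- **Abstract, Methods/Design:** the study is called a pilot. HHS and SPPB are listed as the primary outcomes, and feasibility outcomes are not mentioned.
- **Abstract, Discussion:** the paragraph opens with "This randomized controlled trial will provide evidence regarding the effect of this exercise therapy on physical function and quality of life in older patients after" hip replacement. The hypothesis follows: "both interventions will be effective, but the exercises on the cycle ergometer conferring better results in function, physical performance and quality of life".
- **Objectives and hypotheses:** four aims. The first is "to test the feasibility of undertaking a full trial clinical", the second is "to identify if the cycle ergometer will be well tolerated by older patients with THA in the early phase of rehabilitation" and the third is "to test the feasibility of the proposed outcome measures". The fourth is to obtain an effect size at the end of treatment from which the full trial's sample size can be worked out.
- **Primary outcome measures:** the section opens with feasibility (eligibility, recruitment, retention, completeness of assessments). It then names the between-arm change in HHS and SPPB as the primary clinical outcome and as the primary outcome measure.
- **Statistical analysis:** repeated-measures ANOVA with Tukey comparisons between groups and profile contrasts within groups. "The significance level for statistical tests will be 5"%.
- **Discussion (main text):** feasibility is the main purpose, and the pilot's results will "inform the design of the future definitive study, which would provide evidence relating to the inclusion of this resource".

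**The concern.** A pilot can aim to show that a larger trial can be run, or it can aim to say whether the treatment works. This article says the first in most places and the second in the closing paragraph of its abstract. The two call for different conclusions from the same data.

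The conflict is not confined to one sentence. The abstract's Methods/Design paragraph gives only clinical outcomes as primary. The Statistical analysis section sets a 5% level for its tests and does not say whether they are confirmatory or only support planning. A team that worked from the abstract and the analysis section could fairly report a finding for or against the ergometer. A team that worked from the aims and the main Discussion would report feasibility and a planning estimate. At stake is which of these the published report may claim. A reader of the protocol cannot tell.

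**Working it through.** No arithmetic applies. The article gives no sample size and no power for a stated size, so there is no figure to reproduce. The check is a comparison of the sections on three questions.

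| Question | Efficacy reading | Pilot reading |
|---|---|---|
| What is the trial for? | Abstract, Discussion: evidence on the effect, with a superiority hypothesis | Abstract, Background; Objectives and hypotheses; main Discussion: feasibility |
| Which study yields the evidence? | Abstract, Discussion: this trial | Main Discussion: the future definitive study |
| Which outcomes come first? | Abstract, Methods/Design: HHS and SPPB only | Primary outcome measures: feasibility first, then HHS and SPPB |

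**Step 1: the aims.** Three of the four aims concern feasibility or tolerability. The fourth does involve a treatment effect, but its stated use is to size the next trial. None is to test efficacy. The section title promises hypotheses, yet the section states none. The superiority hypothesis appears only in the abstract.

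**Step 2: the source of the evidence.** The abstract's Discussion paragraph gives the task of providing evidence to this trial. The main Discussion gives evidence on including the ergometer to the later study and gives the pilot the task of informing that study's design.

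**Step 3: the outcomes and the analysis.** The Primary outcome measures section puts feasibility outcomes and a between-arm clinical comparison under one heading, without saying which answers the main aim. The Statistical analysis section compares groups over time at 5% and does not tie those tests to the planning aim. The fourth aim needs an estimate of the effect and its uncertainty, and the role of the tests in meeting that aim is not stated. Nothing in these two sections settles the conflict found in Steps 1 and 2.

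**Step 4: whether one reading dominates.** The abstract's Background, the Objectives and hypotheses section and the main Discussion all support the pilot reading. The abstract's Discussion paragraph is the outlier, so it is the text to bring into line. The outcome and analysis sections then need a short statement of role.

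**The case against.** The strongest reply is that the abstract's sentence is loose but not false. It speaks of evidence on the effect and does not promise to establish efficacy. A randomised pilot that compares HHS and SPPB between arms does yield some evidence, and the fourth aim calls for an effect size. The main Discussion says the definitive study would provide evidence; it does not say that only that study could. The same abstract states the feasibility purpose and calls the study a pilot, and stating a hypothesis does not promise proof.

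Part of this stands. It makes the conflict one of wording and interpretation, with a modest remedy. It does not remove the conflict, because the abstract joins the evidence claim to a superiority hypothesis that appears nowhere among the aims, and the analysis section does not say which reading its tests serve.

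Three stronger readings are tempting, and the article does not support them.

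- **That P < 0.05 will decide the report's conclusion, or that a non-significant result will stop the full trial.** No section sets such a rule. The main Discussion says the results will inform the next study's design and will be submitted for publication whatever they show.
- **That the pilot is shown to be too small to say anything about effect.** No sample size is given, and the full protocol behind the article may hold one. Any power figure would rest on an assumed size, and the answer would depend on which of the article's three effect benchmarks (0.25, 0.75 or 1.25) was used.
- **That HHS and SPPB must stop being primary clinical outcomes.** The Primary outcome measures section already opens with feasibility. The trial is registered and began in August 2011. Removing its primary clinical outcomes would go beyond what the contradiction requires.

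**Conclusion.** The contradiction is real and should be corrected. The abstract's Discussion paragraph claims for this pilot what the main Discussion assigns to the definitive study, and it adds a superiority hypothesis that the aims do not contain. The outcome and analysis sections carry the efficacy reading forward without marking the tests as supporting planning only.

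The consequence is one of interpretation. It bears on how between-arm results for HHS, SPPB, SF-36 and WOMAC may be reported, and it cannot be expressed as a number from what the article states. The conclusion rests only on the article's own text. It assumes no sample size and does not depend on one being absent. It does not say that the planned tests are invalid or that the pilot will be misreported, only that the document permits two incompatible conclusions.

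**What to change.** 1. **Abstract, Discussion.** Replace the evidence claim and the superiority hypothesis with wording such as: *This pilot will report whether a full trial is feasible and will estimate the between-arm differences with 95% confidence intervals to inform the definitive study; it will not conclude on efficacy.*
2. **Statistical analysis.** State that between-arm differences in HHS, SPPB, SF-36 and WOMAC will be reported as estimates with 95% confidence intervals, and that tests at the 5% level are exploratory. This also gives the fourth aim the estimate and uncertainty it needs.
3. **Abstract, Methods/Design, and Primary outcome measures.** State that the feasibility outcomes answer the main aim. Keep HHS and SPPB as the main clinical outcomes.

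The cost is a few sentences of text and the reporting of intervals from data already to be collected. Recruitment, assessments and treatment do not change. The downside is that the sponsor gives up a confirmatory reading of the P values.

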## Background

Total hip arthroplasty (THA) is one of the most frequently performed orthopedic surgeries. Its benefits have been widely documented; in particular, improvements in pain and function in patients with severe hip osteoarthritis (OA) [1-3]. With the worldwide phenomenon of a growing older population, this surgical procedure is being performed more frequently and has consequently increased the number of older patients in rehabilitation [4]. In this context, it becomes necessary to know how this profile of patients responds to the various resources available for rehabilitation in the postoperative period, since the best strategy for a physiotherapy intervention is not clear in the literature [5,6].

After THA, deficits in muscle strength and the limitations on physical function, developed during the evolution of OA, may still be present for many months [7]. Functional deficits in older patients with THA deserve greater attention because they can significantly influence quality of life [8]. The objective of rehabilitation is guided by the early restoration of functional capacity, and this age group, with the physical changes of aging itself, requires a longer time to achieve the desired functional levels [9]. Furthermore, the rehabilitation process also includes the prevention, minimization, and restoration of possible psychological, emotional, and social impacts arising from, and concomitant with, the functional deficits of these patients.

Clinical trials have been proposed to investigate different strategies of rehabilitation after THA [6]. However, few have been conducted exclusively with older patients who have specific physical, psychological, and social characteristics.

Reduced pain and stiffness and increased function have been demonstrated in older patients who received hydrotherapy after THA [10]. The effect of muscle electrical stimulation on quadriceps and triceps surae muscles was investigated in another study of older patients with THA. The addition of this resource to conventional exercise was effective in the recovery of muscle strength of the knee extensors and functional independence of these patients [11]. The inclusion of the ergometer arm in a conventional exercise program also improved pain, stiffness, and function in older patients undergoing THA [12].

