### Interventions

All subjects will receive the same clinical and orthopedic care during hospitalization; that is guidelines for positioning in bed, transfers, limitations of range of motion (ROM) (hip flexion ≤ 90 degrees and hip adduction only to midline) and adaptations in the home (raising the heights of the toilet, bed, sofa, and chairs if necessary).

All subjects will receive a conventional-exercises program. Conventional-exercise sessions will last 50 minutes and be performed 2 days a week for 8 weeks. At the end of the intervention, patients will have performed 16 sessions and will be 10 weeks postoperative.

Under the guidance of a physical therapist, group I will perform cycle ergometer exercises on a vertical, stationary cycle ergometer, Dyamond line, Uniforce Fitness, Dy, model EB 497E ([contact]) (Figure 2) and conventional exercises and group II will perform conventional exercises alone. Ergometer resistance will be minimal (30 W) because the aim is not to perform cardiac exercise. The duration of ergometer cycling will be increased gradually, starting with 10 minutes in the first 2 sessions and increasing to 20 minutes for the remainder, and its aims are to improve coordination, proprioception, ROM, and muscle strength. For this reason, changes are not made during performance of the exercise; frequency is maintained at 60 revolutions per minute and the resistance is also maintained at the starting level. The height of the saddle will be set so that the forefoot will reach the pedal with the knee in minimum flexion (5 to 10 degrees). Special attention will be given to monitoring heart rate and blood pressure before, during, and after exercise. Patients will be instructed to follow the exercises on the cycle ergometer under the supervision of a physiotherapist, ensuring the execution of this only in the presence of the professional.

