**Table 2 Tab2:** **Description of conventional exercises used in total hip arthroplasty rehabilitation**

**Weeks postoperative**	**Lower-limb weight-bearing/Assistive device for walking**	**Description**
2 to 4	Partial/Walker	• Stretching (30 seconds each muscle group): hip flexors, extensors, adductors; knee flexors, extensors; ankle dorsiflexors and plantar flexors
		• Active assisted range of motion (5 to 10 repetitions): hip flexion, extension, abduction, external rotation; knee flexion, extension
		• Muscle strengthening (1 to 3 sets of 10 to 15 repetitions):
		o Hip flexors, extensors, abductors (low-resistance rubber band fixed to the ankle in standing position)
		o Knee extensors (sandbag fixed to the ankle in a seated position)
		• Transfer training: supine to side - lying in bed; sit and stand bed and chair
		• Gait training using a parallel bar and assistive device
4 to 6	Total/Crutch or cane	• Stretching maintained
		• Active range of motion (5 to10 repetitions): hip flexion, extension, abduction, external rotation; knee flexion, extension
		• Muscle strengthening (1 to 3 sets of 10 to 15 repetitions):
		o hip flexors (moderate-resistance rubber band fixed to the ankle in standing position)
		o hip abductors (standing position and seated position with moderate-resistance rubber band)
		o hip extensors (bridge exercise, one- and two-footed in supine position)
		o knee extensors and flexors (weight-training equipment, in a seated position, 20% 1RM)
		• Balance and gait training: walking on an unstable surface, backward walking, side step with the use of parallel bars if necessary
6 to 8	Total/With or without cane	• Stretching maintained
		• Muscle strengthening (1 to 3 sets of 10 to 15 repetitions):
		o hip flexors and abductors maintained
		o hip extensors (bridge exercise, one- and two-footed in supine position with ball)
		• Climbing and descending stairs
		• Coordination, balance, and gait training: circuits with stairs, obstacles, changing direction, changing speed
8 to 10	Total	• All exercises maintained
		• Addition of the muscle strengthening of hip and knee extensors with squat exercises (1 to 3 sets of 10 to 15 repetitions)

RM, repetition maximum.

Description of conventional exercises used in total hip arthroplasty rehabilitation.

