### Intervention and follow-up periods

Assessments will be made at baseline (2 weeks postoperatively), after intervention (10 weeks postoperatively) and at 6-month follow-up (24 weeks postoperatively), and both treatment groups will have completed the intervention after 10 weeks. After the 10 weeks of supervised intervention, patients will be advised to perform some exercises unsupervised at home. In the period between the end of supervised intervention and the final evaluation (at 24 weeks), patients will be able to telephone the physiotherapist for assistance, and there will be a phone contact in the 18th week postoperatively to assess the patients' health condition.

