### Secondary outcome measures

HRQOL will be considered a secondary outcome and the questionnaires used to assess this will be the Medical Outcomes Study 36-Item Short-Form Health Survey (SF-36) [23] as a generic instrument and the Western Ontario and McMaster Universities Osteoarthritis Index (WOMAC) [24] as a specific instrument (measured at the same time points).

The SF-36 is a generic tool for assessing HRQOL that has been translated and validated in Brazil [25]. It consists of 36 items comprising 8 categories: functional capacity (10 items), physical aspects (4 items), pain (2 items), general health status (5 items), vitality (4 items), social aspects (2 items), mental health (5 items) and a question comparing current health conditions with those from a year ago. Each question is assigned a score and the scores tabulated and normalized to a scale of 0 to 100, where 0 corresponds to worst health status and 100 to best health status. There are no cutoff points, and each category is evaluated separately [23,25].

The WOMAC is a specific instrument that measures quality of life in patients with OA of the hip and knee [24]. Its use is indicated for postoperative evaluation of total arthroplasty of the knee (TKA) or hip [26]. The questionnaire was originally intended to be self-administered; however, it has been used for telephone interviews, and recently a computer touch-screen version has been validated. It comprises 24 items divided into 3 categories. The pain category has five questions, the joint stiffness category two questions, and the physical disability category seventeen questions. Each question has five possible answers using a Likert scale representing difficulty, and the responses *none* or *never*, *mild* or *monthly*, *moderate* or *weekly, severe* or *daily*, and *extreme* or *always* correspond to scores of 0, 1, 2, 3 and 4, respectively. Thus, 0 represents the absence of the symptom and 4 the worst manifestation of that symptom. Summing the scores, each category receives a score that is normalized to a scale of 0 to 100 points, with 0 representing the best health status and 100 the worst possible status [24,27].

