## Discussion

The cycle ergometer has been studied as a resource in the rehabilitation of patients with THA and TKA, but with a sample composed of both adults and older people. According to two systematic reviews on the topic, no clinical trials were found that investigated the effect of cycle ergometer-associated exercises with conventional exercises in a group composed exclusively of older patients in the postoperative period after THA [5,6].

When proposing exercise therapies for rehabilitation after THA, it should be considered that the aging process itself brings significant biological, psychological, and social decline. Decreased muscle strength and, depending on other health conditions, serious functional decline can occur [28]. Hip OA can also result in muscle imbalance, pain, and stiffness, which may further compromise function in older patients [29]. Accompanying these physical losses may be impacts on their psychological, emotional, and social aspects of quality of life [30,31].

In patients with severe hip OA, THA aims to relieve pain partially or completely and consequently allow improved function and quality of life [2]. Even considering the risks of a surgical procedure, such as infection, the benefits of THA, when properly indicated, have been demonstrated [1-3,5,6,17]. In this context, patients and professionals seek to achieve the best functional levels in the postoperative rehabilitation period. However, aspects of the rehabilitation of older patients should be considered [31]. The restoration of ROM and muscle strength may be slower because of reduced muscle elasticity and reduced ability to recruit muscle fibers [9,28].

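### The two-arm design can test only the added effect of cycling, so no planned analysis can show that both interventions are effective

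*Protocol article*

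**What the plan says.** The Protocol article's abstract, Discussion paragraph, puts forward a two-part hypothesis. The first part is "If our hypothesis is correct, both interventions will be effective"; the second is that cycling gives better results.

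- **Arms.** Randomization and allocation concealment defines two: cycle ergometer plus conventional exercise, and conventional exercise alone. Under Interventions, "All subjects will receive a conventional-exercises program".
- **Timing.** Intervention and follow-up periods places baseline 2 weeks after surgery, with repeats at 10 and 24 weeks. HHS and SPPB (primary) and SF-36 and WOMAC (secondary) share these times.
- **Analysis.** Statistical analysis plans a repeated-measures ANOVA between groups and times, with Tukey comparisons, and adds "the profile test contrasts to analyze the evolution between assessments in each group". Scores may be ranked if not normal. Primary outcome measures defines the clinical outcome as mean change compared between the arms.
- **Effect of surgery.** Background calls the operation's benefits for pain and function well documented. The main Discussion says that "THA aims to relieve pain partially or completely and consequently allow improved function and quality of life".
- **Weight-bearing.** In Table 2, patients in both arms move from partial loading with a walker (weeks 2 to 4) to "Total/Crutch or cane" in weeks 4 to 6, and later to total loading without an aid.
- **Aims.** Objectives and hypotheses lists four aims: feasibility, tolerability, outcome measures and effect size. Showing that each arm works is not among them.

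**The concern.** Saying that an intervention is effective is a causal claim, and it needs a comparison with patients who did not receive it. This trial has no such patients for the conventional programme, and none for the combined programme taken as a whole. The within-group contrasts are the only planned result a reader could take as support, and they measure everything that happens after week 2, including healing.

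The practical risk is in interpretation. Significant improvement in both arms is likely after hip replacement whatever the exercise does, and the abstract invites reading it as proof that both programmes work. The limitations in the main Discussion cover lack of blinding, discouragement among controls, loss to follow-up and generalizability, but not this.

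**Working it through.** **1. What each comparison identifies**

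- Expected change, group I = recovery + conventional + cycling
- Expected change, group II = recovery + conventional
- Difference between groups = cycling

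Recovery and the conventional programme cancel in the randomized difference. Within either group, recovery and exercise appear only as a sum. No analysis of these two arms can split that sum, and the article supplies no external recovery benchmark. Whether the return to total weight-bearing counts as part of the programme or of recovery does not change this.

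**2. How often recovery alone would look like an effect (illustration)**

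The plan has no figure to reproduce. From the article: the 5% level, and 0.25, 0.75 and 1.25 SD, which it labels small, medium and large effects between groups and which are borrowed here as recovery sizes. Assumed: a two-sided test, true exercise effect zero, equal SDs, 10 to 20 patients per arm, and pre/post correlation ρ of 0.3 to 0.7.

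Paired t-test: d = shift / √(2(1−ρ)), noncentrality = d√n, with n−1 df.

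At n = 15 and shift 0.75:
- ρ = 0.3: d = 0.75/√1.4 = 0.634, noncentrality 2.455, probability 0.627
- ρ = 0.5: d = 0.75/√1.0 = 0.750, noncentrality 2.905, probability 0.771
- ρ = 0.7: d = 0.75/√0.6 = 0.968, noncentrality 3.750, probability 0.936

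| Recovery (SD) | n per arm | ρ = 0.3 | ρ = 0.5 | ρ = 0.7 |
|---|---|---|---|---|
| 0.75 | 10 | 0.433 | 0.562 | 0.778 |
| 0.75 | 15 | 0.627 | 0.771 | 0.936 |
| 0.75 | 20 | 0.767 | 0.889 | 0.984 |
| 0.25 | 15 | 0.119 | 0.147 | 0.214 |
| 1.25 | 15 | 0.967 | 0.994 | >0.999 |

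Both arms significant at n = 15 and 0.75 SD, as the square of the single-arm probability because the arms are independent: 0.393, 0.594, 0.876.

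On ranks (scores ranked over both arms and both times, normal data, 20,000 simulated trials, n = 15, 0.75 SD): one arm 0.60, 0.74, 0.91. The between-arm test rejects in about 5% of trials, as it should.

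**3. Separate point: precision of the between-arm comparison**

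With unit SD, a change score has variance 2(1−ρ) and a week-10 score adjusted for baseline has 1−ρ². The ratio is 2(1−ρ)/(1−ρ²) = 2/(1+ρ), which is 1.54 at ρ = 0.3 and 1.18 at ρ = 0.7. Patients per arm for a between-arm difference of 0.75 SD (two-sided 5%, 80% power, t-based):

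| | ρ = 0.3 | ρ = 0.5 | ρ = 0.7 |
|---|---|---|---|
| Change from baseline | 41 | 29 | 18 |
| Baseline as covariate | 27 | 22 | 16 |

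**The case against.** The strongest reply is that this is half of one sentence in an abstract. The stated aims are feasibility aims, no primary outcome or sample-size step rests on the challenged words, and the other half of the hypothesis is what the design tests. All of that is true. It limits the weight of the point without making the claim testable.

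A second reply is that *effective* may mean only that patients improve, which the within-group contrasts would show. That reading is possible, but the sentence credits the interventions; if improvement is all that is meant, the text should say so. It is also fair that Statistical analysis words the contrasts neutrally and sets no rule that significance proves efficacy. The harm is therefore a likely misreading and not a planned false inference.

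Third, the article does not say how much unaided recovery falls between weeks 2 and 10 on each instrument, and it notes that deficits can last for months. The amount of mixing is therefore unknown, and the illustrative probabilities, from 12% to over 99% at 15 per arm, depend on it. That stands. The identification argument needs none of those numbers.

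Last, covariate adjustment is a different matter from the hypothesis, and repeated-measures ANOVA is a legitimate method. Both are so; it is offered only as a gain in precision.

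**Conclusion.** The concern holds, for the first half of the hypothesis only. The design identifies the added effect of cycling at week 10. It cannot show that the conventional programme, or the combined programme as a whole, is effective, on HHS, SPPB, SF-36 or WOMAC. The between-arm comparison is not biased by this.

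That conclusion follows from the arms and the timing of baseline. How often it would mislead rests on assumed recovery, sample size and correlation: with 0.75 SD of shared recovery and no exercise effect, both arms of 15 would be significant in 39% to 88% of trials. For a feasibility pilot this is a modest point, worth correcting because the sentence is prominent and the correction is cheap.

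**What to change.** 1. In the abstract's Discussion paragraph, limit the hypothesis to the difference between arms, or say that both groups are expected to improve.
2. In Statistical analysis, state that the within-group contrasts describe recovery.
3. Add to the limitations in the main Discussion that change from week 2 includes surgical recovery and the return to total weight-bearing, so it cannot show that either programme works.

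These are wording changes in three places. The downside is that the paper can no longer claim that the conventional programme itself works; since that is not one of the four aims, the pilot loses nothing it set out to learn.

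Separately, for precision, compare week-10 scores between arms with the baseline score as covariate, ranking both if scores are ranked. Treat week 24 the same way, but state that controls are offered the ergometer after week 10, so week 24 is not a clean contrast of cycling with no cycling. This needs no extra visits, patients or forms. Baseline leaves the repeated-outcome vector, so within-group change must be summarised separately, as means with intervals. The pre/post correlation needed to size the full trial can still be estimated from the same data.
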